## Methods

### Study design and procedures

We will conduct this randomized controlled trial to examine the efficacy of an animation game in improving both satisfaction and behavioural changes among current and potential visitors to Japan. The participants will complete the survey online. The participants will answer a questionnaire on the satisfaction and behavioural changes prior to and after participating in one of two interventions. We will evaluate the changes in their satisfaction and motivation levels (Fig. 1).

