### Outcomes

The primary outcome of this study is the difference in the average or median CSQ-8 (8-item Client Satisfaction Questionnaire) [29] score between the participants who will have played the *Sa-Chan* game and controls immediately after the interventions. We will assess the outcome using a self-administered questionnaire, the CSQ-8 scale, which has been used widely for health education [29] and has been shown to have reliable and valid in previous research [30]. The CSQ-8 is an eight-item questionnaire that uses a four-point Likert scale and will be used to assess the respondent’s level of satisfaction regarding the health care system and safety in Japan. The total score ranges from 8 to 32. A high score denotes greater satisfaction. The reliability of the questionnaire will be examined by Cronbach’s alpha.The second outcome of the study is the difference in motivation between the participants who will have played the *Sa-Chan* game and the controls immediately after the interventions. We will ask one question, “Are you likely to follow this information yourself”, and the participants will respond using a four-point Likert scale to determine whether they will change their behaviour or assess their level of motivation to follow the Japanese health-related guidelines. We will collect the data before and after the interventions. We will evaluate the data with the Information-Motivation-Behavioural Skills model [31]. This model has been used in a number of risk reduction behaviour studies [32].The third outcome is whether the participants understood the information presented in the *Sa-Chan* game. When a participant understands the information corresponding to each of 15 items, he or she will respond with “yes” to the item. The questions will be related to both interventions. If a participant understands how to deal with the following topics in Japan, he or she might choose correct answers.

In total, the questionnaire that will be used to assess the outcomes in (1), (2), and (3) and performing the intervention will take less than 10 min to complete. The participants will be visitors or individuals who wish to visit Japan.

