#### Data analysis

For the primary outcome of this study, we will analyse the difference in the median scores for the CSQ-8 recorded before and after the intervention between groups with the Wilcoxon signed-rank test. To compare the pre- and post-intervention scores between groups, the Wilcoxon rank-sum test will be used. We will adjust for other potential demographic factors that might affect the results of the multiple regressions.For the secondary outcome, regarding motivation, we will compare the differences in the pre- and postintervention scores for the behavioural change question between groups with the Wilcoxon rank-sum test.The third outcome is related to the participant’s understanding of the *Sa-Chan* game, which includes health knowledge questions. We will determine whether the answers are related to the characteristics of the participants.

All data analyses will be conducted using the JMP statistical package (version 14.0). The answers provided for the open-ended questions about Japanese health information will be examined by word-frequency analysis, with involves a word relationship network and co-occurrence, using the language analysis software Text Mining Studio (version 6.2) [33].

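### As printed, the motivation item refers to information not yet shown at baseline, and its definition (post score) does not match its planned test (pre-to-post difference)

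*Protocol article*

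**What the plan says.** The Outcomes section of the protocol article defines the secondary outcome in these terms: "The second outcome of the study is the difference in motivation between the participants who will have played the" game and the controls, assessed straight after the interventions. It gives a single item, "Are you likely to follow this information yourself", and explains that "the participants will respond using a four-point Likert scale to determine whether they will change their behaviour" or to gauge their motivation to follow Japan's health guidance. It then adds: "We will collect the data before and after the interventions".

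The Study design and procedures section gives the same timing: "The participants will answer a questionnaire on the satisfaction and behavioural changes prior to and after participating in one of two interventions". It states the aim as the "efficacy of an animation game in improving both satisfaction and behavioural changes".

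For the test, the Data analysis section says: "we will compare the differences in the pre- and postintervention scores for the behavioural change question between groups with the Wilcoxon rank-sum test".

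The Sample size section gives 1002 participants for a difference of 0.178 in the questionnaire score with SD 1.0, 80% power and alpha 0.05. It does not mention the motivation item.

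**The concern.** Two things do not fit together.

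- **The baseline stem.** The item asks about information that, as far as the article describes, participants first meet in the game or the control animation. Before viewing, a respondent has nothing definite to answer about. The pre and post answers then need not measure the same thing, and their difference has no clear meaning.
- **The endpoint.** One section defines a post-intervention comparison and another appears to test a change score. These are different variables for the same outcome, and as written either could be reported.

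There is also a smaller point. Differencing a four-point ordinal item treats a move from 1 to 2 as equal to a move from 3 to 4, a spacing that the scale does not guarantee.

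At stake are what the secondary result means and how precisely it is estimated.

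**Working it through.** **Inputs from the Sample size section:** total N 1002, difference 0.178, SD 1.0, alpha 0.05, power 80%.

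**Assumptions:** 1:1 allocation (501 per arm), a two-sided test, equal pre and post SDs, and a pre-post correlation ρ. The documents give no ρ, so a range is shown. Applying 0.178 SD to the motivation item is also an assumption.

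**Step 1: reproduce the plan's figure.** n per arm = 2(1.960 + 0.842)² × 1.0² / 0.178² ≈ 496, so 992 in total. A t-test calculation gives 497 per arm, 994 in total. Both are close to 1002. A one-sided calculation gives 782 and does not reproduce it. Power at 501 per arm: 0.178 × √(501/2) = 2.817; 2.817 − 1.960 = 0.857; Φ(0.857) = 80.4%.

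**Step 2: compare three analyses.** The SD is 1 for the post score, √(2(1 − ρ)) for the change score, and √(1 − ρ²) for the post score adjusted for baseline in a linear model. Power = Φ(2.817/SD − 1.960).

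| ρ | Change-score SD | Change score | Post score alone | Post score, baseline-adjusted |
|---|---|---|---|---|
| 0 | 1.414 | 51.3% | 80.4% | 80.4% |
| 0.3 | 1.183 | 66.3% | 80.4% | 84.0% |
| 0.5 | 1.000 | 80.4% | 80.4% | 90.2% |
| 0.7 | 0.775 | 95.3% | 80.4% | 97.6% |

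The change score loses to the post score below ρ = 0.5, equals it there, and beats it above. At the same ρ, adjustment is never worse than the change score, because 1 − ρ² = (1 − ρ)(1 + ρ) ≤ 2(1 − ρ).

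**Step 3: check on a four-point item.** This simulation used 501 per arm, 2000 runs, a normal latent variable with assumed cut-points −1.2, −0.3 and 0.8, a latent shift of 0.178, and the rank-sum test. Here ρ is the latent correlation.

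| ρ | Change score | Post score | Type I error, change score |
|---|---|---|---|
| 0 | 41% | 75% | 4.95% |
| 0.3 | 54% | 73% | 4.95% |
| 0.5 | 68% | 75% | 5.35% |
| 0.7 | 85% | 73% | 5.65% |

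The pattern is the same, with the crossover between 0.5 and 0.7. The mean between-arm difference was about 0.15 scale points for both scores, so the change score is noisier or less noisy depending on ρ, but not biased.

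**The case against.** The strongest reply is that no bias arises. Baseline precedes the randomised exposure, so even a poorly understood baseline answer has the same expected distribution in both arms. A reader might infer that the planned comparison is uninterpretable. That does not follow: the between-arm test keeps its type I error and its expected mean difference. What lacks clear meaning is the baseline answer and the within-person change.

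A reader might also infer that power is necessarily lost. The documents do not support that either. It depends on a correlation they do not give. A low value is plausible for a question about something unseen, but a general tendency to agree could correlate the two answers. The 80% benchmark was not set for this item.

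Three further replies have weight:

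- The article condenses the full protocol, and the questionnaire is not shown. A baseline lead-in about Japan's health guidance in general, which the Outcomes section names as the target of motivation, cannot be excluded. As printed, though, one stem is given for both time points.
- Subtraction is the likeliest reading of "compare the differences in the pre- and postintervention scores for the behavioural change question between groups", not the only one. The phrase could mean a between-group comparison at each time point. That ambiguity is itself a reason to fix the sentence.
- A reader might infer that the trial will claim changed behaviour. The article mostly calls this outcome motivation and is open that it is one question asked straight after viewing. The behavioural label is loose wording.

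A ceiling argument adds little: someone who answers 4 beforehand cannot improve, but the post score is capped at 4 too.

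**Conclusion.** The point holds in a limited form. As printed, the baseline stem has no referent, and the outcome definition and the test do not match. The consequence is an unclear estimand for a secondary outcome and a possible loss of precision, not bias or an invalid test.

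The size depends on ρ: relative to the post score, the change score ranges from 29 percentage points less power at ρ = 0 (80.4 − 51.3) to 15 points more at ρ = 0.7 (95.3 − 80.4). This rests on 501 per arm, a two-sided 5% test, equal SDs and a borrowed 0.178 SD effect.

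The recommendation does not depend on knowing ρ. The adjusted post score has at least the change score's power at every ρ computed, and it matches the Outcomes section's own definition. The adjusted figures come from a linear model and describe a baseline item with the stated correlation; a reworded item may have a different one.

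**What to change.** 1. In Data analysis, name the post-intervention motivation score as the secondary endpoint, compared between arms as Outcomes defines it, and do not subtract the pre-intervention answer. The rank-sum test can stay for an unadjusted comparison.
2. If a baseline is kept, reword it so that it can be answered before viewing, for example by asking how likely the respondent is to follow health and safety guidance when visiting Japan. Enter it as a covariate, for example in a proportional-odds model. If the questionnaire already has such a lead-in, state it.
3. Describe the result as stated motivation or intention, in Study design and procedures as well as in Data analysis.

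The cost is one question stem and one analysis sentence, plus the change of label, with no extra data. The downside is small: there would be no within-person change on an identically worded item.

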#### Other information

We will also include in this randomized controlled study basic characteristics of the participants, such as their previous visits to Japan, sex, age, and educational level. We will determine whether the distributions of these characteristics are balance between the two groups and identify factors that might influence the results. We conducted a pilot test with 13 participants at a college in New York on August 12, 2018.

### Bias prevention

The allocation of participants to either the control or the intervention group will be blinded to both the participants and the researchers.

#### Data analysis

For the primary outcome of this study, we will analyse the difference in the median scores for the CSQ-8 recorded before and after the intervention between groups with the Wilcoxon signed-rank test. To compare the pre- and post-intervention scores between groups, the Wilcoxon rank-sum test will be used. We will adjust for other potential demographic factors that might affect the results of the multiple regressions.For the secondary outcome, regarding motivation, we will compare the differences in the pre- and postintervention scores for the behavioural change question between groups with the Wilcoxon rank-sum test.The third outcome is related to the participant’s understanding of the *Sa-Chan* game, which includes health knowledge questions. We will determine whether the answers are related to the characteristics of the participants.

All data analyses will be conducted using the JMP statistical package (version 14.0). The answers provided for the open-ended questions about Japanese health information will be examined by word-frequency analysis, with involves a word relationship network and co-occurrence, using the language analysis software Text Mining Studio (version 6.2) [33].

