### Interventions

#### Intervention

The intervention group will watch a five-minute digital game titled *Sa-Chan Game* in English (Table 1). This animation is in the format of a quiz that aims to provide information on the health care system and safety in Japan for overseas visitors. Its content is based on the results of a previous study on overseas visitors’ concerns about visiting Japan [14]. It starts with Asian music and contains 11 items. We will share the animated game through a website.

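### Understanding, the third outcome, is analysed only against participant characteristics and not between the randomised arms, and its scoring wording is inconsistent

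*Protocol article*

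**What the plan says.** The Outcomes section of the protocol article lists three outcomes. The first is the CSQ-8 score, defined as a difference between those who played the game and controls. The second is framed the same way: "The second outcome of the study is the difference in motivation between the participants who will have played the" game and the controls. The third is framed differently: "The third outcome is whether the participants understood the information presented in the" Sa-Chan game.

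On how the third outcome is measured, the same section says: "When a participant understands the information corresponding to each of 15 items, he or she will respond with" a yes to that item. It then says "The questions will be related to both interventions", and that someone who understands how to deal with the topics "he or she might choose correct answers".

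The Data analysis section assigns a Wilcoxon rank-sum test between groups to the CSQ-8 and another to motivation. It describes the third outcome as understanding of the game, "which includes health knowledge questions", and gives one analysis for it: "We will determine whether the answers are related to the characteristics of the participants".

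**The concern.** Randomisation protects a comparison between arms. It does not protect a comparison between, say, older and younger participants or first-time and repeat visitors. Relating the answers to characteristics may describe who reports understanding, but it says nothing about the effect of the game relative to the animation. The article names a between-arm test for the other two outcomes and a different kind of analysis for this one, so the gap lies in what is stated and is not merely detail left out.

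The wording adds two problems. First, the outcome is tied to information in the game, while controls watch *Mari Info Japan*; read literally, it is unclear whether controls contribute. Second, answering yes because one understands is a self-report, whereas correct answers and knowledge questions imply a test. These measure different things and support different conclusions.

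At stake is what the trial can report about conveying information. Satisfaction and motivation are both self-ratings. If the 15 items turn out to have right answers, understanding would be the only one of the three outcomes that tests what participants took in.

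**Working it through.** The point rests mainly on comparing the Outcomes and Data analysis sections, outcome by outcome.

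| Outcome | Framed as a difference between arms? | Stated analysis |
|---|---|---|
| CSQ-8 satisfaction | Yes | Includes a rank-sum test between groups |
| Motivation | Yes | Rank-sum test between groups |
| Understanding, 15 items | No; understanding of the game | Relation to participant characteristics only |

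**Do the characteristics include arm?** The Other information section lists previous visits, sex, age and educational level as examples. It uses them to check balance between the groups, so arm is not one of them.

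**Is the randomised comparison possible?** The questions are said to relate to both interventions. Provided controls answer the same 15 items, which that sentence implies, the data will exist in both arms.

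**Is the scoring settled?** There are three descriptions: a yes per item, correct answers, and health knowledge questions. The first is a self-rating and the other two imply a key. The article states neither a key nor a total.

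**Does the fix bear on the sample size?** The plan's own figure is checked first. Inputs from the Sample size section are a difference of 0.178, SD 1.0, alpha 0.05, 80% power and a total of 1002. Two-sided testing and 1:1 allocation are assumed, as neither is stated.

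- n per arm = 2 × (1.960 + 0.842)² × 1.0² / 0.178² = 496 after rounding up, or 992 in total, close to 1002.
- Power at 501 per arm = Φ(0.178 / √(2/501) − 1.960) = Φ(0.857) = 0.80.

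The figure reproduces. It was set for the questionnaire score, not for understanding, so adding a secondary comparison leaves it unchanged. It does not guarantee power for understanding. As an illustration for one item, with 501 per arm and assumed control proportions of 50%, 60%, 70% and 80% (the documents give none):

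| Difference between arms | 50% | 60% | 70% | 80% |
|---|---|---|---|---|
| 10 points | 0.89 | 0.91 | 0.96 | 0.99 |
| 5 points | 0.35 | 0.37 | 0.43 | 0.55 |

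**Why one total and not 15 item tests?** Fifteen separate tests at 0.05 would carry a familywise error of 1 − 0.95¹⁵ = 0.54 if the items were independent. Correlated items would give a different figure, but the reason for a single pre-stated total remains.

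**The case against.** The best defence is that the trial's stated aims are satisfaction and motivation or behavioural change, that the third outcome is worded descriptively, and that a descriptive analysis matches it. Fuller detail may also sit in a document not shown. Part of this stands: the plan makes no explicit claim that the game teaches better, and the outcome ranks third. But the article does state an analysis for this outcome, in a randomised trial, with questions said to fit both arms, and that analysis does not use the randomisation.

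A second objection is that if a yes is only a self-rating, comparing arms would not show which one teaches better. That is right, and it limits the interpretation. The comparison would still be a valid randomised comparison of perceived understanding.

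A reader might also infer more than the documents support:

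- *That some questions are untaught.* Each intervention has 11 items (of the game: "It starts with Asian music and contains 11 items") and 15 are asked. One content item can feed several questions, the two content tables are not reproduced in the text at hand, and the questions are said to relate to both interventions. The difference in counts shows nothing.
- *That anyone who agrees with everything gets full marks.* This holds only if yes is the scored answer throughout. The items are not shown and no total is defined.
- *That keying some items to no is a cheap repair.* If the items ask whether a topic is understood, this would mean rewriting the instrument.

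**Conclusion.** The point holds in a limited form. The only stated analysis of understanding is a non-randomised association, although the between-arm comparison appears to be available. The scoring wording needs to be reconciled.

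One of three outcomes is affected, and not the primary. The sample size, the satisfaction and motivation analyses and the primary conclusion are untouched. It would go too far to say that the trial cannot tell whether the game conveys information better: that describes the plan as written, not the design. If the items prove to be self-ratings, even the added comparison would speak to perceived understanding and not to knowledge.

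The conclusion assumes that controls answer the same 15 items, as the Outcomes section implies. It needs no figure from outside the documents; the item-level powers above are illustrations on assumed proportions.

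**What to change.** 1. Define the third outcome for both arms, as understanding of the health and safety information covered by the interventions, and remove the tie to the game alone.
2. Pre-state one total over the 15 items and compare it between randomised arms, reporting the difference with a 95% confidence interval.
3. Keep the association with participant characteristics, labelled exploratory.
4. Reconcile the scoring text in the Outcomes and Data analysis sections. If a yes is a self-rating, report the result as perceived understanding and not as knowledge. If the items have right answers, score them against the key and fix that key before the data are seen.

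The cost is one added secondary analysis on answers the questionnaire already yields, plus a few sentences of definition. No change in sample size and no rewriting of items is needed.

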## Discussion

The study will offer a unique digital education strategy in the form of the game *Sa-Chan* to overseas visitors to stay healthy and safe. To welcome visitors from other nations, the host country needs to provide practical and useful information in an attractive and effective manner.

## Data Availability

Not applicable.

## Abbreviations

COVID-19: Coronavirus Disease 2019
CSQ-8: 8-item Client Satisfaction Questionnaire
Trials UMIN-CTR: University Hospital Medical Information Network Center Clinical Trials Registry
RCT: Randomized controlled trial
